## Abstract

**Background:**

Falls are a significant public health problem. Thirty to fifty percent of the elderly of 65 years and older fall each year. Falls are the most common type of accident in this age group and can result in fractures and subsequent disabilities, increased fear of falling, social isolation, decreased mobility, and even an increased mortality. Several forms of exercise have been associated with a reduced risk of falling and with a wide range of physiological as well as psychosocial health benefits. Tai Chi Chuan seems to be the most promising form of exercise in the elderly, but the evidence is still controversial.

In this article the design of a randomized clinical trial is presented. The trial evaluates the effect of Tai Chi Chuan on fall prevention and physical and psychological function in older adults.

**Methods/Design:**

270 people of seventy years and older living at home will be identified in the files of the participating general practitioners. People will be asked to participate when meeting the following inclusion criteria: have experienced a fall in the preceding year or suffer from two of the following risk factors: disturbed balance, mobility problems, dizziness, or the use of benzodiazepines or diuretics. People will be randomly allocated to either the Tai Chi Chuan group (13 weeks, twice a week) or the no treatment control group.

The primary outcome measure is the number of new falls, measured with a diary. The secondary outcome measures are balance, fear of falling, blood pressure, heart rate, lung function parameters, physical activity, functional status, quality of life, mental health, use of walking devices, medication, use of health care services, adjustments to the house, severity of fall incidents and subsequent injuries. Process parameters will be measured to evaluate the Tai Chi Chuan intervention. A cost-effectiveness analysis will be carried out alongside the evaluation of the clinical results. Follow-up measurements will be collected at 3, 6 and 12 months after randomization.

**Discussion:**

As far as we know this is the first trial in Europe considering Tai Chi Chuan and fall prevention. This project will answer a pragmatic research question regarding the efficacy of Tai Chi Chuan regarding fall reduction.

## Background

Thirty to fifty percent of the elderly of 65 years and older fall each year [1,2]. About twenty percent of them need medical care after a fall and about six percent of the accidents result in a fracture. Moreover falls can result in disabilities, increased fear of falling, social isolation, decreased mobility and even an increased mortality [3,4]. The risk to fall is strongly related to previous falls, disturbed balance, dizziness, decreased muscular strength, use of benzodiazepines and diuretics and changes in walking pattern [5,6]. Based on these prognostic factors it is feasible to identify elderly who are at risk for falling.

To prevent fall incidents in the elderly exercise programs may be useful. In the most recent Cochrane review [2] on the effectiveness of interventions to prevent fall incidents and in the meta-analysis of the FICSIT (Frailty and Injuries: Cooperative Studies of Intervention Techniques) trials [7] the effectiveness of different exercise programs in healthy elderly populations were examined. In both the review and the meta-analysis exercises seem to have a positive effect to prevent fall incidents, although the evidence is limited. In addition, reviews of Verhagen et al. [8] and Li et al. [9] show that the evidence is still weak for the effect of Tai Chi Chuan in preventing falls, improving balance and improving cardiovascular function.

Tai Chi Chuan is a traditional Chinese exercise that has been practiced for many centuries. It is an integral part of the Traditional Chinese Medicine. It consists of a series of movements (positions) that are performed in a slow and flowing manner. The Tai Chi positions operate on three basic principles. First, the body should be extended and relaxed. Second, the mind must be alert and calm. Last, all body movements require well-coordinated sequencing of segments. The accent is on relaxation and balance control. In the literature many beneficial effects of Tai Chi Chuan are reported, such as improved balance, decreased fall incidents, decreased blood pressure, and increased self-efficacy [9].

Although promising, it is not entirely clear yet whether Tai Chi Chuan can indeed prevent fall incidents in the elderly. Only in one trial it is found to reduce the risk of multiple falls by 47,5% [10]. Since the evidence is still controversial we decided to conduct this study evaluating the effect of Tai Chi Chuan on fall prevention and physical and psychological function in older adults in the Dutch situation.

## Methods/Design

### Study design

This study is a randomized, partially blinded, clinical trial to assess the effectiveness of 'usual care' and Tai Chi Chuan compared to 'usual care' only on fall prevention in the elderly living at home with an increased risk for falling. 'Usual care' means that people can use or apply for all available services in the area. Figure 1 presents the flow diagram of the study design. The Medical Ethics Review Committee at Erasmus MC, University Medical Center Rotterdam, approves the study.

**Figure 1 F1:**
[figure not shown]
Study design.

### Study population

General practitioners (GPs) will be informed by mail in Dordrecht and Zwijndrecht (two towns in the west of the Netherlands) about the background and the goal of our research. Using a response fax they can indicate if they are willing to participate or not. If we do not receive a response within a week or after sending a reminder, we will phone them to get clear if they are willing to participate. An appointment will be made with the participating GPs in order to identify eligible people from their patient databases. Eligible are all people of seventy years and older living at home who are at risk for falling. We will select on the basis of in- and exclusion criteria as shown in table 1.

**Table 1 T1:** Inclusion and exclusion criteria

***Inclusion criteria***
- 70 years and older
- living at home
- at least one self-reported fall accident in the preceding year or at least two of the following self-reported risk factors for falling: disturbed balance, mobility problems, dizziness or the use of benzodiazepines or diuretics
***Exclusion criteria***
- progressive disorders:
• neurological disorders (e.g. Parkinson's disease, Alzheimer's disease, multiple sclerosis, epilepsy, grand stroke with rest symptoms, polyneuropathy)
• metastatic/terminal cancer or undergoing a treatment for cancer
- unable to undergo the intervention (e.g. confined to bed, restricted to a wheelchair, unable to walk for eight meters without help, unable to reach the location). These items are stated by the GP after inclusion criteria are checked by phone.
- unable to fill in a Dutch questionnaire
- not available for measurements or intervention or knowing in advance to miss eighty percent of the lessons
- received Tai Chi Chuan in the preceding year

Potential eligible people will receive an information package with detailed information on the study from their GP. Using the included response form they can sign up, ask for additional information or withdraw. In case of withdrawal, people will be kindly requested to write down the reason. In case of willingness to participate they will be asked to sign an informed consent form. A postage free envelope will be included. Reminders will be sent after four weeks.

### Telephone questionnaire

After returning the response form, potential participants will be interviewed by phone. This serves as the screening instrument for final eligibility (see table 1) and partly as baseline measurements. Participants are again informed on the randomization procedures, allowing them another opportunity to reconsider participation before study entry. Potential participants will be asked which study group they prefer to be enrolled in, to evaluate whether patient preferences might influence outcome. Finally, participants will be invited to a location near their homes to conduct the remainder of the baseline measurements.

### Baseline measurements

The baseline measurements consist of the following items. Sociodemographic factors (age, gender, ethnicity, marital status, education, composition of household), physical characteristics (e.g. height, weight, acuity of vision), environmental factors (e.g. pets, adjustments to the house), use of walking devices, medication, and use of health care services (e.g. GP, specialist, physiotherapy, home care/district nurse).

At baseline the following secondary outcome measures are measured: Balance (Berg Balance Scale), fear of falling (The Falls Efficacy Scale), physical parameters (blood pressure and heart rate at rest, FEV1 (i.e. forced expiratory volume during the first second) and PEF (i.e. peak expiratory flow)), physical activity (Physical Activity for the Elderly), functional status (Groningen Activity Restriction Scale), quality of life (EuroQol), and mental health (SF-36). For further details see 'Secondary outcome measures'.

### Sample size and power

The effect of Tai Chi in decreasing fall incidents is conservatively estimated on 25 percent [10]. A power calculation (alpha = 0,05; beta = 0,1; drop out percentage of twenty percent) estimates that 135 participants are needed in each study group. This implies that we intend to enroll 270 participants in total.

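### The stated 90% power with 135 per group has no support in the protocol article; on the natural reading it requires about 80% of controls to fall within the year

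*Protocol article*

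**What the plan says.** The Sample size and power section sets the effect: "The effect of Tai Chi in decreasing fall incidents is conservatively estimated on 25 percent", citing one earlier trial. It then fixes the size: "A power calculation (alpha = 0,05; beta = 0,1; drop out percentage of twenty percent) estimates that 135 participants are needed" in each group, 270 in all. It does not say what proportion of controls is expected to fall, how many falls per person are expected, or with what SD. It also does not say whether 25 percent is relative or absolute, which test was assumed, or whether alpha is one- or two-sided.

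The Background gives the only annual fall risk in the document: "Thirty to fifty percent of the elderly of 65 years and older fall each year". It reports of the cited trial that "it is found to reduce the risk of multiple falls by 47,5" percent.

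The Abstract makes the number of new falls the primary outcome. The Statistical analyses section compares it by Student's t-test and survival techniques. Table 1 restricts entry to people of 70 and over with a fall in the past year or at least two risk factors.

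**The concern.** The 90% is the trial's only statement of what it can detect, and a reader cannot check it because the control rate is missing. When the missing input is solved for, the answer is a fall risk well above anything the document quotes. If the true control risk is lower, the trial has materially less power than stated. A non-significant result from a trial described as 90% powered for a 25% reduction is likely to be taken as evidence against such a reduction, when the design may have had little better than an even chance of detecting it.

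**Working it through.** **Inputs from the Sample size and power section:** alpha 0.05, power 0.90, dropout 20%, effect 25%, 135 per group. Evaluable per group: 135 × 0.8 = 108.

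**Assumptions supplied here:** two-sided test (z = 1.960 and 1.2816), outcome the proportion with at least one fall in the year, 25% taken as relative (p2 = 0.75 × p1). The relative reading is the natural one: the estimate is called conservative beside a 47.5% reduction in risk.

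**Step 1. Reproduce 135.** With p̄ the mean of p1 and p2, pooled formula:

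n = [1.960·√(2p̄(1−p̄)) + 1.2816·√(p1(1−p1) + p2(1−p2))]² / (p1−p2)²

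At 80% vs 60%, p̄ = 0.70: [1.960·√0.42 + 1.2816·√0.40]² / 0.20² = (1.270 + 0.811)² / 0.04 ≈ 108.2. Dividing by 0.8 gives 135.3. (Rounding up to 109 first gives 137, so the match is close but depends on rounding.) Solving for the control risk at n = 108 gives 80.1% two-sided and 75.0% one-sided.

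**Step 2. Power at other control risks.**

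Power = Φ{[(p1−p2)√n − 1.960·√(2p̄(1−p̄))] / √(p1(1−p1) + p2(1−p2))}

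Example, 50% vs 37.5%, n = 108: (1.299 − 1.375)/0.696 = −0.109, so power is 46%.

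| Control risk | Power, 108 per group | Power, 135 per group | Enrolled per group for 90% | Relative reduction detectable with 90% power, 108 per group |
|---|---|---|---|---|
| 50% | 46% | 54% | 412 | 43% |
| 60% | 60% | 70% | 289 | 36% |
| 70% | 76% | 84% | 202 | 31% |
| 80% | 90% | 95% | about 135–137 | 25% |

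**Step 3. Absolute reading.** A drop of 25 percentage points needs at most 82 evaluable per group without continuity correction (at 62.5% vs 37.5%), or 82/0.8 ≈ 102 enrolled. It never gives 135. At 50% vs 25% it needs 77 evaluable, or 97 enrolled.

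**Step 4. Number of falls, by t-test.** n = 2(1.960 + 1.2816)²(SD/Δ)², with (1.960 + 1.2816)² = 10.507. At n = 108, Δ/SD = √(2 × 10.507/108) = 0.441. With Δ = 0.25 × control mean, SD/mean = 0.25/0.441 = 0.57. For comparison, a Poisson count with mean 1 has an SD equal to its mean.

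**Step 5. Number of falls, by rate ratio 0.75.** n = 10.507 × [(1/m + k) + (1/(0.75m) + k)] / (ln 0.75)², where m is the control mean per year, k the dispersion and (ln 0.75)² = 0.0828. Pure Poisson (k = 0) at n = 108: m = 10.507 × 2.333/(108 × 0.0828) ≈ 2.7 falls per control person-year. Any overdispersion raises this. At an assumed m = 1, power is 50% for k = 0, 37% for k = 0.5 and 30% for k = 1.

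**The case against.** **The stated power has not been shown to be wrong.** This stands. The section does not disclose its control rate, and the published number is recovered closely at 80% vs 60%. A reader might infer an arithmetic slip; the document does not support that.

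**The 30–50% belongs to another population.** This also stands. It describes people of 65 and over in general, the sample-size section does not use it, and the Background itself ties fall risk to the very factors used for selection. A reader might put 30%, 40% and 50% into the formula and report power of 24%, 34% and 46% as the trial's power. That is not supported, because the enrolled group should fall more often. But a higher risk alone is not enough: at 70% power is still 76%.

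**Other readings could rescue the figure.** An absolute 25-point effect would leave 108 per group with more than 90% power, but it does not yield 135. At 50% control risk it would be a 50% relative reduction, larger than the 47.5% against which 25% is called conservative. A one-sided test still needs 75% of controls to fall.

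**Survival analysis.** A reader might set a hazard ratio of 0.75, find that about 508 first falls are needed, and conclude that 270 people can never suffice. That treats a different effect. Under constant hazards, 80% vs 60% corresponds to ln 0.4/ln 0.2 = 0.57, which needs about 132 events, while 0.70 × 216 ≈ 151 would be available. Nor are the survival techniques limited to first falls.

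**Dropouts may still contribute data**, given the intention-to-treat analysis. With all 135 evaluable, power is 54%, 70% and 84% at 50%, 60% and 70%: better, but below 90%.

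**A journal article condenses.** A fuller protocol may state the rate. But the article publishes its own sample-size section with a power claim, and the implied assumption sits far from the only risk printed beside it.

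**Conclusion.** The point holds in a limited form: the 90% power cannot be reproduced from the article, and no fall risk it states supports it. On a two-sided comparison of fallers with a 25% relative reduction and 108 evaluable per group, the figure needs about 80% of controls to fall. Over control risks of 50–80%, power runs from about 46% to 90%. On the stated primary outcome, the requirement is an SD of about 0.57 of the control mean for the t-test, or about 2.7 falls per control person-year for a Poisson comparison.

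These results rest on assumptions the document does not confirm: effect scale, sidedness and, for the fallers calculation, a binary stand-in for a count. If the sponsor did assume about 80% fallers and can justify it for this population, one sentence settles the matter.

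**What to change.** Keep 270 participants and revise the Sample size and power section to:

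1. State the assumed control fall risk or rate (with the SD if a t-test is the basis), its justification for the selected population aged 70 and over, whether 25% is relative or absolute, the test and its sidedness.
2. Replace the single 90% with power over a justified range of control risks (for example 50–80%, about 46–90%), or with the relative reduction detectable with 90% power (about 43% at 50%, 36% at 60%, 31% at 70% and 25% at 80% control risk).
3. Say that a non-significant result will be interpreted from the confidence interval and will not be read as excluding a 25% reduction.

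The cost is rewording and a less favourable stated power. No extra participants or measurements are needed.

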### Randomization

After baseline measurements participants will be assigned to one of the four strata based on gender (male/female) and the prognostic factor fall accidents in the preceding year (yes/no). An independent research assistant will perform randomization into either the control or the intervention group using a randomization list generated by a computer. To avoid unequal group sizes a block randomization will be used using block sizes of four. When two persons live together (e.g. married couples) they will be allocated to the same group, i.e. the group to which the first person contacted is allocated to, in order to avoid contamination.

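### Previous falls are used only as a threshold; a pre-specified 0/1/2/3+ covariate would be a cheap gain in precision for the number of falls

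*Protocol article*

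**What the plan says.** - **Prognosis.** The Background section states "The risk to fall is strongly related to previous falls, disturbed balance, dizziness, decreased muscular strength" and goes on to name medication use and changes in gait.
- **Eligibility (Table 1).** A person qualifies with "at least one self-reported fall accident in the preceding year". The alternative route needs no fall, only two of a list of risk factors: "disturbed balance, mobility problems, dizziness or the use of benzodiazepines or diuretics".
- **Randomization.** There are four strata, formed by gender and "the prognostic factor fall accidents in the preceding year (yes/no", with blocks of four.
- **Outcome.** The abstract states: "The primary outcome measure is the number of new falls, measured with a diary".
- **Baseline data.** The Baseline measurements section lists no number of previous falls. The telephone interview covers the eligibility items, but the article does not say whether it asks how many falls there were.
- **Analysis.** Statistical analyses plans a Student's t-test and survival techniques for falls. Effect estimates are adjusted only if a clinically relevant baseline difference in prognosis is present. The form of any covariate is not stated.

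**The concern.** The outcome counts the same event as the baseline predictor. A participant with one fall last year and a participant with six share a stratum, and nothing in the article tells them apart. Two consequences follow.

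First, some variance in next year's count that the number of previous falls could explain stays in the error term. Adding the yes/no stratum to a model would recover only part of it.

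Second, adjustment depends on seeing a baseline difference. Stratification keeps yes/no close to balanced, so a check on yes/no will rarely show one. The imbalance that can still arise by chance is in recurrent fallers within the yes stratum, and yes/no cannot reveal it.

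**Working it through.** The article gives no figure for the precision lost, so there is none to reproduce. Everything below except the 270 participants and the eligibility rule is an assumption.

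**Model.** Each person has a fall rate drawn from a gamma distribution with mean μ and shape a. Previous-year and next-year falls are independent Poisson counts given that rate. Everyone with at least one previous fall is eligible, and a share q of non-fallers enters through the risk factors. For a person with x previous falls:

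- expected falls next year: (a + x) · μ/(a + μ)
- variance next year: that mean × [1 + μ/(a + μ)]

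**Worked case: μ = 1, a = 1, q = 0.2**

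1. Before selection, 0, 1, 2 and 3+ falls have probability 0.5, 0.25, 0.125 and 0.125. Multiplying the first by 0.2 gives a total of 0.1 + 0.25 + 0.125 + 0.125 = 0.6. The enrolled shares are 0.167, 0.417, 0.208 and 0.208, so 83% are in yes.
2. Expected falls next year are (1 + x)/2: 0.5, 1.0, 1.5, and 2.5 for 3+ (mean x of 4). The overall mean is 1.333 and the mean in yes is 1.5.
3. Variance between yes and no: 0.167 × 0.833² + 0.833 × 0.167² = 0.139.
4. Variance between the four categories: 0.167 × 0.833² + 0.417 × 0.333² + 0.208 × 0.167² + 0.208 × 1.167² = 0.451.
5. Total variance: the mean within-person part is 1.5 × 1.333 = 2.0. The part explained by x is Var(x)/4 = 2.222/4 = 0.556. The sum is 2.556.
6. R² is 0.139/2.556 = 0.054 for yes/no and 0.451/2.556 = 0.177 for the categories. Yes/no keeps 0.054/0.177, about 31%.
7. Equivalent participants: 270 × [(1 − 0.054)/(1 − 0.177) − 1] ≈ 40, or 15%.

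**Range.** The same calculation with other inputs (q = 0.2 to 0.4):

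| μ | a | R² yes/no | R² 0/1/2/3+ | Equivalent participants |
|---|---|---|---|---|
| 0.6 | 2 | 0.02–0.03 | 0.05 | 6–7 |
| 1 | 1 | 0.05–0.09 | 0.18–0.20 | 38–40 |
| 1.5 | 0.5 | 0.09–0.14 | 0.31–0.35 | 87–89 |

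Over all the scenarios run, the gain is about 5 to 89 participants.

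**Less favourable assumptions.** The model takes each person's rate as unchanged from year to year and recall as perfect. If 30% of people draw a new rate and 20% of past falls are forgotten, the central gain (μ = 1, a = 1) falls to 15–17 participants, about 6%. The range falls to about 2–39. In these and the other runs yes/no mostly keeps less than half of what the categories explain, but in some it keeps more.

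**Hidden imbalance.** In the worked case half of the previous fallers had two or more falls (0.25/0.5). They average 2.0 falls next year, against 1.0 for those with one. About 270 × 0.833 = 225 people are in yes, or 112.5 per group. The between-group difference in the recurrent share among them has standard deviation √(0.5 × 0.5 × 2/112.5) = 0.067, about 7 percentage points.

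**The case against.** The strongest reply is that nothing in the Randomization section is wrong. Two binary factors with blocks of four are an ordinary choice, and precision comes from the analysis rather than from the strata. That stands, and the strata should stay as they are.

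It can also be said that an article need not list every interview question or covariate coding. The number may already be recorded, and the full protocol or analysis plan may define the covariate. So the threshold-only use is a statement about this article, not about the trial. What the article does fix is a t-test with adjustment conditional on observed imbalance, and that plan leaves the information unused unless an imbalance is seen.

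The gain is measured against a model containing yes/no, which the article does not plan. This is fair. It isolates what the number of falls adds, and it applies to mean counts rather than directly to the survival techniques.

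A reader might infer three stronger claims that the documents do not support:

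- **That the eligibility rule puts most participants in yes.** There is a second route without a fall and no share is given. With 20–100% of non-fallers qualifying, the simulated share in yes ran from 29% to 86%.
- **That previous falls are the strongest predictor.** The Background section lists them with other factors and does not rank them.
- **That most of the precision is lost.** Compared with the full count, yes/no kept 24–66% of the explained variance, so this depends on the scenario.

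**Conclusion.** The point holds as a cheap improvement, not as an error in the randomization. The article names previous falls as strongly related to fall risk and takes the number of falls as its outcome, but uses the predictor only as a threshold. It makes adjustment depend on observed imbalance. Yes/no leaves part of the available precision unused, often about half or more of what the categories would explain. The gain beyond yes/no is about 5–89 of 270 participants, or about 2–39 under the less favourable assumptions. These sizes rest on assumed gamma-Poisson falls, an assumed mean and dispersion, and an assumed share of non-fallers enrolled. The direction is firm; the size is not.

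**What to change.** 1. Keep yes/no for stratification.
2. Record the number of falls in the preceding year (0, 1, 2, 3 or more) in the existing telephone interview, or use it if it is already recorded.
3. In Statistical analyses, pre-specify these categories as a covariate in the primary model for number of falls, regardless of observed imbalance. The count comparison then becomes a regression model in place of the bare t-test.
4. Show the categories in the baseline comparison of the groups.
5. Place people screened without a number in a category for one or more falls, number unknown. Set this before allocation is disclosed.

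The cost is one answer field (none if the number is already held) and one covariate definition. Randomization, visits and treatment do not change. The Time plan shows that people had already been screened and included and that the first group started in February 2004. For anyone in the number-unknown category the covariate is yes/no again, so the gain shrinks with the share of such participants.

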### Intervention group

Participants in the intervention group will receive in addition to the 'usual care' Tai Chi Chuan lessons.

The Tai Chi Chuan form is based on the one used by Wolf et al. [11]. This form turned out to be appropriate for the elderly because all components of movement that typically become limited with aging are emphasized. The ten positions are easily comprehensible. It is derived from the Yang style and consists of a form with ten positions: 1. Opening; 2. Grasping the Sparrow's Tail, Left; 3. Grasping the Sparrow's Tail, Right; 4. Cloud Hands; 5. Repulse Monkey; 6. Part Wild Horse's Mane; 7. Brush Knee Twist Step; 8. Lift Kick Left; 9. Lift Kick Right; 10. Closing. The ten positions are linked together in a continuous, smooth-flowing form.

Four Tai Chi Chuan-teachers are available to give the lessons. All are qualified to give the lessons and are experienced in working with elderly. Together they will develop and finalize the Tai Chi Chuan-protocol.

In the literature [8] the recommended frequency of lessons varies from once a day to once a week during a period ranging from 10 weeks to one year. We thought the most optimum and practicable frequency is twice a week for thirteen weeks. Each lesson will last one hour, starting with twenty minutes warming-up and ending with ten minutes cooling down. Hereby Chi Kung exercises will be used. Chi Kung means 'control or mastery of the breath'. Emphasis is placed on relaxation and on contemplation of the breath. In addition to the lessons the participants will be asked to practice the learned Tai Chi Chuan positions at home at least twice a week for about fifteen minutes.

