### Statistical analyses

To assess if randomization was successful, descriptive statistics of baseline characteristics will be used. In case clinically relevant baseline differences regarding prognosis of future incidence of falls is present, effect estimates will be adjusted using multivariate analysis.

Dropouts are defined as participants who stop participating during the first three months (i.e. intervention period). Non-compliers are defined as participants who miss more than twenty percent of the lessons.

The analysis will be performed using the intention-to-treat principle, e.g. all patients are included as randomized irrespective of compliance. Missing values are assigned the last available valid score.

We will evaluate the effect of the intervention in reducing the number of fall incidents using the Student's t-test and survival techniques. To analyze the secondary outcome measures the Student's t-test, the Mann-Whitney test or the Chi-square test will be used according to the type of variable.

When drop out is higher than fifteen percent and/or the compliance is lower than seventy percent an additional per-protocol analysis will be carried out. These are restricted to those participants who complied fully with the intervention protocol and outcome measures.

At the end of the analyses the allocation of participants will be disclosed.

A cost-effectiveness analysis will be conducted alongside the analysis of the clinical data.

Direct costs (such as medication, additional therapy, visits to health care providers) as well as indirect costs (such as disability) measured by the EuroQol, will be related to the primary outcome measure (fall incidents).

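### People who live together are allocated as a pair but analysed as independent individuals, and the second partner's arm can be known before entry; the likely effect on error rates is modest

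*Protocol article*

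**What the plan says.** All references are to the protocol article.

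- **Allocation.** Randomization follows the baseline measurements, in four strata (gender by fall in the preceding year) with blocks of four. For cohabitants there is an exception: "When two persons live together (e.g. married couples) they will be allocated to the same group", that is, "the group to which the first person contacted is allocated to". The reason given is avoidance of contamination.
- **Analysis.** Under Statistical analyses, falls are compared "using the Student's t-test and survival techniques". Secondary outcomes are compared with the t-test, Mann-Whitney test or chi-square test, depending on the type of variable. No household term is named. Multivariate adjustment is foreseen only if clinically relevant baseline differences appear.
- **Sample size.** The listed inputs are "alpha = 0,05; beta = 0,1; drop out percentage of twenty percent" and a 25 percent effect. No design effect is among them.
- **Entry and masking.** Under Study population, consent is requested with the response form, and reminders go out after four weeks. Under Telephone questionnaire, people may reconsider before study entry and are asked which group they prefer. Under Masking, participants are unmasked.

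**The concern.** The second member of a pair gets no allocation of their own, so a pair does not supply two independent randomised observations. Partners share a home, its hazards and daily habits, and a positive correlation in falls, activity or quality of life is plausible. The named tests count each person separately. With positive correlation they understate the variance, so intervals are too narrow and p-values too small.

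The second issue is concealment. Nothing requires both partners to be fully enrolled before the first is allocated. If they enter one after the other, the second can learn the arm at home and decide whether to go on in that knowledge. That would be selection after allocation, in a trial that itself regards group preference as a possible influence on outcome.

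**Working it through.** **1. The plan's own figure.** The article "estimates that 135 participants are needed in each study group". With 20% dropout this leaves 135 × 0.8 = 108 evaluable per group. The 135 cannot be rebuilt from the stated inputs, because no control rate, standard deviation or sidedness is given. That is a separate matter. Here the stated 90% power at 108 per group is taken as given, with a two-sided 5% test assumed.

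**2. Design effect for pairs.** Let f be the share of participants who belong to a co-allocated pair and ρ the within-pair correlation. Among N people there are fN/2 pairs, and each adds 2ρσ² to the variance of the sum:

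Nσ² + (fN/2)(2ρσ²) = Nσ²(1 + fρ), so DE = 1 + fρ.

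**3. Consequences.**
- True type I error = 2[1 − Φ(1.96/√DE)]
- True power, if the test is corrected = Φ[(1.96 + 1.2816)/√DE − 1.96]

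The article states neither f nor ρ, so both are assumptions.

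| f | ρ | DE | SE multiplier | Type I error | Power |
|---|---|---|---|---|---|
| 0.10 | 0.02 | 1.002 | 1.001 | 5.0% | 89.9% |
| 0.20 | 0.10 | 1.02 | 1.010 | 5.2% | 89.4% |
| 0.30 | 0.20 | 1.06 | 1.030 | 5.7% | 88.3% |
| 0.40 | 0.30 | 1.12 | 1.058 | 6.4% | 86.5% |
| 0.50 | 0.30 | 1.15 | 1.072 | 6.8% | 85.6% |

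Worked row: f = 0.30 and ρ = 0.20 give DE = 1.06 and 1.96/√1.06 = 1.904, so the type I error is 5.7%.

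**4. An opposing effect.** Allocation is stratified on prior falls, which the Background calls strongly related to fall risk. An unadjusted t-test ignores the balance this creates, and its standard error then tends to be too large. As a rough guide, if the strata explain a share R² of the outcome variance and the two effects multiply, they cancel when R² = 1 − 1/DE. For DE = 1.06 that is 5.7%; for DE = 1.15 it is 13.0%. The article gives no R².

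**5. Sequence of entry.** The stated order for one person is consent form, telephone screen with a chance to reconsider, baseline, allocation. For a pair, the article says only that the second person follows the first. It sets no condition that links the first person's allocation to the second person's consent or baseline. Joint entry and staggered entry both fit the text. Only joint entry is safe.

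**The case against.** **The pair effect may be close to nothing.** A pair counts only if both partners are 70 or older, at risk of falling, free of the exclusions and willing, so the pair share could be low. This stands: the lower end of the range is indistinguishable from 5%. It is also why one cannot say that the reported intervals will be too narrow. The stratification effect works the other way, and the net direction for the unadjusted t-test is not established.

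**Model detail belongs in an analysis plan that is not shown.** This is partly right. Survival techniques can include robust or shared-frailty models, so that wording does not conflict with the design. The t-test, Mann-Whitney test and chi-square test are named outright, however, and they do conflict with the allocation rule.

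**Foreknowledge is not a described procedure.** Correct. The wording about the first person contacted also fits two people already identified together from the general practitioner's files. What remains is that the text leaves the possibility open.

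**The forced allocation upsets the gender strata.** A husband and wife do fall in different strata, and the second takes no draw from the list. The imbalance is likely to be slight, and adjustment for gender and prior falls deals with it.

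**A stronger reading: clustering by Tai Chi class.** A reader might infer that group teaching in one arm does more damage. With assumed classes of 10-15 and an ICC of 0.02-0.05, the variance factor [1 + 1 + (m − 1)ICC]/2 is 1.09-1.35, and the type I error 6.0-9.2%. The documents do not support this as a finding. They say "Four Tai Chi Chuan-teachers are available to give the lessons" and imply group delivery elsewhere, but give no class size or ICC. Apart from cohabitants, people are randomised individually, and if Tai Chi has no effect on anyone, class membership should add no correlation in falls. Lessons also fill only 13 weeks of a year's fall recording. Class effects bear more on generalising across teachers and classes than on the validity of the test.

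**Conclusion.** The concern holds in a limited form. The tests named for the t-test, rank and chi-square comparisons do not respect the unit of allocation for cohabiting pairs. If partners are positively correlated, the variance is understated by a factor of about 1.00-1.15, and the type I error rises from 5% to about 5.0-6.8% before any offset from stratification. These figures rest on an assumed pair share of 10-50% and a correlation of 0.02-0.30. The effect is modest and could not by itself overturn a clear result. Separately, the article permits, without prescribing, a sequence in which the second partner knows the arm before entering. Its size cannot be estimated from the documents. Both points are worth correcting because correction is cheap.

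**What to change.** **Analysis.** Record a household identifier. For primary and secondary outcomes, use regression with household-clustered (robust or GEE) standard errors, adjusted for gender and prior falls; for time to fall, use a survival model with household-robust variance. The number of clusters is ample: 270 × (1 − f/2) gives about 202 households at f = 0.50 and about 256 at f = 0.10. Adjusting for the strata also removes the opposing bias in the standard error.

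**Allocation.** Randomise each household once, only after all participating members have consented and completed baseline, and state which member's stratum supplies the draw. The Time plan shows that inclusion had already begun. For households already allocated, record each partner's dates of consent, baseline and allocation, and report how many second partners entered after the first was allocated.

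**Class clustering.** At most a sensitivity analysis, with a partially nested model and a small-sample correction. At 10-15 per class, 135 people form only about 9-14 classes (135/15 = 9; 135/10 = 13.5), too few for uncorrected sandwich errors.

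**Cost.** A few lines of analysis wording, one linked identifier, slightly wider intervals if partners are correlated, and a short wait for the second partner's baseline.
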